### **3.3 Exclusion criteria**

- Current insulin use
- Recent routine HbA1c on record  $\geq 12\%$
- Weight loss of  $>5\text{kg}$  within the last 6 months
- Recent eGFR on record  $<30 \text{ mls/min/1.73}^2$
- Substance abuse
- Known cancer
- Myocardial infarction within previous 6 months
- Severe or unstable Heart Failure defined as equivalent to the New York Heart Association (NYHA):
  - Grade 3 - marked limitation of physical activity. Comfortable at rest, but less than ordinary activity causes fatigue, palpitation, or breathlessness, and
  - Grade 4 - unable to carry out any physical activity without discomfort. Symptoms of cardiac insufficiency at rest. If any physical activity is undertaken, discomfort is increased.
- or**
- Grade 2 if symptoms are not attributed to obesity - Slight limitation of physical activity. Comfortable at rest, but ordinary physical activity results in fatigue, palpitation, or breathlessness
- Learning difficulties
- Not fluent in English language
- Current treatment with anti-obesity drugs
- Diagnosed eating disorder or purging
- Pregnant/ considering pregnancy

- Patients who have required hospitalisation for depression or are on antipsychotic drugs
- People currently participating in another clinical research trial
- People with metal implants or devices and those who have claustrophobia cannot take part as MR scans are needed as part of the study

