## **4 Trial procedures**

Patients will all be seen at the Glasgow Clinical Research Facility for all appointments.

Patients randomised to control will be advised to continue with usual care for 3 months before coming back to receive the intervention. They will be asked not to aim to lose any weight during the initial control period, but rather to wait until they commence the intervention part of the study. An appointment will be given to the patient for 3-months' time, and they will commence the intervention at that point.

Patients randomised to intervention will commence Counterweight Plus, which includes a TDR phase followed by structured food reintroduction. This will be delivered by research Dietitians experienced in programme delivery.

**TDR phase (0 to 12-20wks):** A commercial micronutrient-replete 825-853kcal/d LELD will be provided (Cambridge Weight Plan) to replace normal foods, with ample fluids, for 12-20 weeks. Oral hypoglycaemic agents (OHA), antihypertensive and diuretic drugs will be withdrawn on commencement of TDR, and reintroduced (according to guidelines) if diabetes or hypertension returns. Aspirin will be continued in patients prescribed this because of a previous MI (prior to the previous 6 months), but will be discontinued in patients who are prescribed it purely because they have T2D. Beta-blockers will be continued in patients prescribed these for the management of angina. A soluble fibre supplement (Fybogel 2x3.5g/day) will be prescribed to avoid constipation.

Participants will return for review one week after commencement on the TDR and at 2 weekly intervals thereafter till week 12-20 (total of 7-13 appointments) and the commencement of the food reintroduction stage.

To allow some flexibility for patients whose commitments, or practical limitations vary, the TDR phase will be permitted to continue up to 20 weeks if they fail to lose >15kg by week 12. Any patient whose BMI falls below 22 kg/m^2, before week 12 will be moved forward to 'food reintroduction and weight maintenance'. Reasons for moving to food reintroduction prior to week 12 will be recorded.

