### **Appt 1: Week 0+1**

#### **Intervention Participants**

- Measurement of weight, blood pressure and capillary blood glucose (measured by blood glucose meter) recorded
- Oral hypoglycaemic, antihypertensive and diuretic medications discontinued
  - Aspirin only discontinued in patients who are prescribed it purely because they have T2D.
  - Beta-blockers continued in patients prescribed these for the management of angina.
- Commence TDR phase of intervention as per Counterweight Plus Appointment Planner (App C)
  - Fybogel supplement prescribed
- Appointment made for next visit

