## **Appendix E: Protocol for management of blood pressure**

### ***Background***

Antihypertensive and diuretic drugs will be stopped on the day the total diet replacement is commenced.

This is a safety measure, because blood pressure is likely to fall on the diet.

This protocol lays out the standard approach to be followed to allow clear description of the research findings. Individual clinical decisions may be necessary for a person's best interest.

The level of 140mmHg is chosen to allow safe decisions during the weight loss period. After the Food Reintroduction period follow usual guidelines for management of hypertension.

To simplify decision making, systolic pressure only is used as a guide to therapy even though both systolic and diastolic are relevant to long term benefit.

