### ***Protocol***

#### ***When antihypertensive drugs are stopped, re-emphasise the importance of avoiding sodium (salt)***

1. In the first 2 weeks after stopping antihypertensives and diuretics:  
If systolic BP over 165 mmHg on repeated measurement - restart one drug, as below.
2. Thereafter, if systolic BP is >140 mmHg - restart one drug as below.
3. Increase dose weekly to achieve target.
4. If systolic BP remains >140mmHg on the first drug - add a second drug, as below.
5. Increase dose weekly to achieve target.
6. Repeat as necessary with third, fourth or more drugs (increasing each to maximum dose).

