#### ***Order of reintroduction of previously used drugs***

1. ACE inhibitors (ramipril, lisinopril, perindopril, etc)
2. Angiotensin receptor blockers (irbesartan, candesartan etc)
3. Thiazide type (bendroflumethazide, indapamide etc)
4. Spironolactone
5. Calcium channel blocker (nifedipine, amlodipine etc)
6. Beta blocker (atenolol, labetalol etc)
7. Alpha blocker (doxazosin, prazosin)
8. All others

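### Antihypertensives and diuretics are stopped by drug class at the start of TDR, with no written exception for those taken for heart failure or after MI

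*Protocol*

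**What the plan says.** **Withdrawal.** Section 4 (TDR phase) states that "antihypertensive and diuretic drugs will be withdrawn on commencement of TDR, and reintroduced (according to guidelines) if diabetes or hypertension returns". The synopsis, section 4.1 (Appointment 1) and Appendix E repeat the withdrawal of antihypertensives, and the last two also name diuretics. None of these statements refers to why the drug was prescribed.

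**Exceptions.** Section 4.1 has "Beta-blockers continued in patients prescribed these for the management of angina", and section 4 says the same. Aspirin is handled separately: section 4 keeps it after an earlier MI and stops it when type 2 diabetes is the only reason for it.

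**Restart.** Appendix E uses systolic pressure only. For the first two weeks the trigger is a repeated reading above 165 mmHg. After that: "Thereafter, if systolic BP is >140 mmHg - restart one drug as below". Drugs come back singly, following a list headed "Order of reintroduction of previously used drugs", which ranks eight classes. A further drug is added only if systolic pressure stays above 140 mmHg.

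**Eligibility.** For heart failure, section 3.3 excludes NYHA grades 3 and 4, and "Grade 2 if symptoms are not attributed to obesity". For infarction it excludes "Myocardial infarction within previous 6 months".

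**Discretion.** The Background of Appendix E adds: "Individual clinical decisions may be necessary for a person's best interest".

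**The concern.** The eligibility criteria and the drug rule do not fit together. A patient with an older MI or mild heart failure may enter while taking an ACE inhibitor, a beta-blocker, spironolactone or another diuretic for that condition. The protocol then treats the drug as if it had been given for blood pressure: it is stopped with the rest and comes back only if systolic pressure rises.

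The protocol already accepts that indication matters, because it checks indication for aspirin and for beta-blockers in angina. Its aspirin rule also shows that participants with an earlier MI were expected. Such a participant keeps aspirin but, under the same paragraph, loses the ACE inhibitor, and the beta-blocker too unless it is for angina.

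What is at stake is the safety of a small eligible subgroup, not the feasibility endpoints or the estimates. Control participants start the intervention after three months, so the rule can reach both arms.

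**Working it through.** No power or precision figure is involved. The check sets the provisions side by side, then counts the time under the rule.

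**1. Who can enter** (section 3.3)

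| Condition | Excluded | Still eligible |
|---|---|---|
| MI | within 6 months | more than 6 months ago |
| Heart failure | NYHA 3 and 4; NYHA 2 not due to obesity | NYHA 1; NYHA 2 with symptoms attributed to obesity |

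**2. What happens to their drugs** (sections 4 and 4.1)

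| Drug and indication | Rule |
|---|---|
| Aspirin after MI | continued |
| Beta-blocker for angina | continued |
| Beta-blocker for heart failure, or after MI without angina | stopped |
| ACE inhibitor or angiotensin receptor blocker for heart failure or after MI | stopped |
| Spironolactone or other diuretic for heart failure | stopped |

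**3. How they come back** (Appendix E). The trigger is systolic pressure, although the appendix justifies withdrawal with "This is a safety measure, because blood pressure is likely to fall on the diet". By the protocol's own expectation, the trigger may never fire. If it does, the order is by class: ACE inhibitor 1st of 8, spironolactone 4th, beta-blocker 6th. A diuretic that is neither thiazide-type nor spironolactone falls into the last class, 8th.

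**4. A worked case.** Take a participant with an MI more than six months ago and no angina, on an ACE inhibitor and a beta-blocker.

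- If systolic pressure stays at or below 165 mmHg for two weeks and at or below 140 mmHg after that, neither drug returns.
- If it rises above 140 mmHg and settles on the ACE inhibitor, the beta-blocker does not return.
- The beta-blocker returns only if pressure remains above 140 mmHg on the ACE inhibitor.

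In none of these cases does the reason for prescribing the drug decide whether it returns.

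**5. Time under the rule**

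- Standard schedule: drugs stop at Appointment 1 (week 0+1) and the final visit is Appointment 11 (week 0+19), so 19 − 1 = 18 weeks.
- Protocol limits: TDR up to 20 weeks plus food reintroduction up to 8 weeks, so 20 + 8 = 28 weeks.
- It is shorter if BMI falls below 22 kg/m² before week 12, because the participant then moves on early.

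**6. Number affected.** The documents give no prevalence of older MI, mild heart failure or use of these drugs, so no count or event rate can be derived.

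**The case against.** The strongest reply has five parts.

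- **Written discretion.** Appendix E calls itself the standard approach and allows individual clinical decisions, which would let a clinician keep a drug. That is true. But the sentence names no drug or condition and requires no check, and the authors did not rely on it for aspirin or angina, where they wrote explicit exceptions.
- **Guideline-based restart.** Sections 4 and 5 both refer to guidelines for reintroduction. Section 4 ties this to the return of diabetes or hypertension. Section 5 ties it to monitoring of blood pressure and postural symptoms. Neither covers a drug needed at normal pressure.
- **GP screening.** GPs remove unsuitable patients from the search lists before invitation (sections 3.1 and 3.4). This is a real safeguard before any drug is stopped, but it is not a check of each drug's indication, and people who answer a media advert contact the study team directly.
- **A narrower reading.** The restart condition and the title of Appendix E suggest that only drugs given for hypertension were meant. However, an angina exception would be unnecessary on that reading, and diuretics are named without qualification.
- **Size.** The group is small. Obesity-attributed grade 2 symptoms are weak evidence of heart failure treatment, and the exclusion of metal implants or devices may remove some cardiac patients. The 28 weeks combines two maxima and exceeds the six-month treatment duration in the synopsis. It is time under the rule, not time shown to be off needed treatment. All of this stands and limits the importance of the point.

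Discussion of risks with the GP (section 5) and the recording of events and hospitalisations (section 9 and Appendix F) also help, but they act after a problem appears.

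**Conclusion.** The concern holds. The list of exceptions is incomplete for patients whom section 3.3 admits, and the restart rule is tied to a measure unrelated to why their drug was prescribed. The exposure is 18 weeks on the standard schedule and up to 28 at the limits, for a number of participants that is unknown, probably small and possibly zero.

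The conclusion rests on reading the withdrawal rule by drug class, as it is written, and on the possibility that an eligible patient takes such a drug. It does not assume that continuing every drug is right on a low-energy diet, and it claims no rate of harm. Confidence is medium. The change should be made because it is cheap and concerns safety, and because the study is meant to inform a larger trial in which the same rule would reach more such patients.

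**What to change.** 1. Record the indication of each antihypertensive and diuretic at Appointment 0.
2. Limit the automatic withdrawal, and the systolic restart rule in Appendix E, to drugs prescribed for hypertension.
3. Require that any drug prescribed for heart failure or after MI, including one that also treats hypertension, be reviewed with its prescriber before Appointment 1. The review may still decide to reduce or stop it.
4. Write this beside the aspirin and angina exceptions in sections 4 and 4.1, and refer to it in Appendix E.

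The cost is a short amendment to these three places and one field in the baseline practitioner workbook. The downside is that a few participants need individual handling, so drug withdrawal becomes slightly less uniform.

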| Primary Objective:   | To determine the feasibility and acceptability of an intensive weight management programme in South Asian patients to achieve remission of diabetes at 3 months.                                                                                                                                                                                                                                                                                                                                                                                                                                                                                                                                                                                                                                                                                                                                                                                                                                                                                                                                                                                                                                                                                                                                                                                                                                                                                                                                                                                                                                                                                                                                                                                                                                                   |

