| Primary Endpoint:    | Percentage achieving $\geq 15$ kg weight loss, and/or HbA1c $< 48$ mmol/l, off treatment, at end Total Diet Replacement stage to inform larger randomised controlled trial                                                                                                                                                                                                                                                                                                                                                                                                                                                                                                                                                                                                                                                                                                                                                                                                                                                                                                                                                                                                                                                                                                                                                                                                                                                                                                                                                                                                                                                                                                                                                                                                                                         |

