| Rationale:           | 
This proposal is for a small pilot study in South Asian patients,, essentially identical to the protocol used by the same research team in the Type 2 diabetes Remission Clinical Trial (DiRECT) study in Caucasian patients, which has now completed recruitment of 290 patients. Published research in people of European origin demonstrates that low/very low energy diets achieving around 15 kg weight loss usually lead to diabetes remission, after 8 weeks of treatment. The Diabetes Remission Clinical Trial (DiRECT) is currently underway in Tyneside and Scotland to assess long-term outcomes of this treatment approach in primary care. However, to date research has not been conducted using this approach with patients of South Asian origin. South Asians are typically diagnosed with Type 2 diabetes 5-10 years younger, with a briefer period of 'prediabetes', and at a lower body mass index than white Europeans. For any given BMI, South Asians have higher fat mass and a larger proportion of fat mass in deep intra-abdominal visceral depots and in ectopic sites: there is emerging evidence for greater liver and pancreas fat, driving type 2 diabetes. This is potentially reversible, but conventional weight management methods commonly achieve less weight loss among South Asians. The proposed study will assess if an existing evidence-based weight management programme, 'Counterweight-Plus', is acceptable to patients of South Asian origin and achieves weight change and reversal of T2DM compared with routine care. The Primary focus being acceptability of TDR in this population and response in terms of weight change and remission of diabetes following the TDR. Initial findings will be used to inform a larger randomised controlled trial.
 |

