| Product, Dose, Modes of Administration: | 
The intervention to be assessed is an 825-853kcal/day TDR, planned to be followed for 12 weeks, with stepped food reintroduction, using a tested energy-restricted nutritionally balanced (30% fat, <10% saturated fat) weight loss maintenance diet using food-group exchanges, plus support to increase physical activities to approach 15,000 steps/day if individually acceptable) with 30 minutes brisk-walking daily. Both intervention and control arms will continue to receive standard care under current clinical guidelines for T2DM. The intervention will be delivered by research dietitians who are trained and competent in Counterweight Plus. Process evaluation will be conducted to assess the number of patients invited, the number who engage with the programme, and completion and attrition rates. Participants will be asked to give written feedback on the programme. Assessments of quality of life, weight loss expectations, and psychological process measures will be made. Mechanistic studies will also be conducted to investigate the changes in pancreatic and liver fat. Participants will be offered the option of undergoing measurements of MR and body composition. These data will inform a larger randomised controlled trial.
 |

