#### **4.1 Study schedule (App A)**

##### **Appointment (Appt) 0: Baseline (All Patients)**

- Review and discuss study participation
- Review inclusion/exclusion criteria including readiness to change screening
- Secure informed consent
- Assign study ID
- Measurement of: height, weight, waist & hip circumference & blood pressure
  - Weight measured using study scales and printout of weight countersigned by practice nurse/dietitian and CW specialist
  - Three blood pressure readings recorded 2-3 minutes apart
  - Waist and hip not measured if BMI>35kg/m^2

Venepuncture for:

- HbA1c, urea and electrolytes, glucose, insulin, liver function tests, lipids.)\*. All Fasting Sample, as per Sample Handling Manual (App C)
- Pregnancy test in women of childbearing years
- Questionnaire completion: EQ-5D, Participant Expectation and Psychological Process Questionnaire
- Randomise patient to CONTROL or INTERVENTION
- Completion of practitioner workbook by research dietitians
- Appointment made for MRI Scan

- Arrange appointment for MR, body composition and appetite hormones measurements if participant has consented to these.
- **INTERVENTION ONLY:** Samples of TDR products given to patients to allow choice of product to be used during intervention to be made.
  - **CONTROL ONLY:** Advised to continue with usual care as per current guidelines. Appointment made for 3 months for repeat
  - measurement of MR, body composition and appetite hormones,
  - MRI scan and venepuncture for HbA1c, urea and electrolytes, glucose, insulin, liver function tests,
  - commencement of weight management intervention

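### The primary endpoint is read at the end of total diet replacement, whose length depends on the endpoint's own 15 kg criterion, so for participants who extend it is not the 3-month result named in the objective

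*Protocol*

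**What the plan says.** - **Objective and endpoint (Synopsis).** The primary objective concerns feasibility and acceptability of the programme "to achieve remission of diabetes at 3 months". The primary endpoint is the percentage with at least 15 kg loss and/or HbA1c below 48, "off treatment, at end Total Diet Replacement stage to inform larger randomised controlled trial". The rationale adds that the study will assess whether the programme "achieves weight change and reversal of T2DM compared with routine care".
- **Length of TDR.** The Synopsis describes TDR as "planned to be followed for 12 weeks". Section 4 heads the phase as running to weeks 12-20 and states that "the TDR phase will be permitted to continue up to 20 weeks if they fail to lose >15kg by week 12". The Appointment Planner (Appendix C, Appointment 7) likewise tells the practitioner to continue TDR up to 20 weeks when more than 15 kg has not been lost. In the other direction, a participant whose BMI drops under 22 "before week 12 will be moved forward to" food reintroduction (Section 4).
- **Control reading.** For controls, the Appointment 0 list reads "Appointment made for 3 months for repeat" bloods (including HbA1c) and MRI, after which they start the diet. Footnote c of Appendix A agrees.
- **Blood timing.** Appendix A ticks bloods at week 0+12. Section 4.1 (Appointments 2-7) treats week 12 and end of TDR as one occasion. Section 4.3 says end of TDR.
- **Drug withdrawal.** Section 4 stops glucose-lowering drugs when TDR starts. The Appointment 1 list (week 0+1) has "Oral hypoglycaemic, antihypertensive and diuretic medications discontinued". Section 4.2 defines remission as requiring at least 3 months off such drugs.

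**The concern.** The rule that sets when the endpoint is read is practically the endpoint's own weight threshold (more than 15 kg in one place, at least 15 kg in the other). A participant who passes it at week 12 is read then. One who misses it may be given up to 8 more weeks to pass, on weight or on HbA1c. A lean participant may be read before week 12, with less time to reach 15 kg. The percentage therefore mixes readings taken at times that depend on how the participant was doing.

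Two things follow. The percentage is meant to inform a larger trial, and the objective invites the reader to take it as a 3-month response, which it is not for extenders. And any randomised comparison on this endpoint would set intervention readings at up to week 20 against control readings at about week 13. No later control reading exists, because controls have by then begun the diet. For an extender it is also unclear whether HbA1c is taken at week 12, at end of TDR or both. If it is not taken at week 12, the 3-month glycaemic status cannot be recovered later.

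**Working it through.** **Inputs.** Section 6.1 gives an example mean loss of 8 kg, an SD of 6 kg for change over 3 months, and n = 20. The 15 kg threshold is from the Synopsis. The extension of up to 20 - 12 = 8 weeks is from Section 4. The document gives neither uptake nor rate of loss during the extension, so both are assumptions shown as ranges.

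**The plan's own figure.** Margin of error = t(0.975, 19 df) × 6/√20 = 2.81 kg. This reproduces the stated 2.8 kg and confirms that the SD refers to a 3-month change in 20 people.

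**Week 12, weight criterion only.** Take week-12 loss as Normal(8, 6). P(loss ≥ 15) = 1 - Φ((15 - 8)/6) = 0.122, or 2.4 of 20. The remaining 0.878, or 17.6 of 20, are eligible to extend.

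**End of TDR, weight criterion only, all eligible extending for 8 weeks.**
- Low end, 0.1 kg/week: 8 × 0.1 = 0.8 kg is added, so a week-12 loss of 14.2 kg is enough. P = 0.151.
- A fraction f of the participant's own first-12-week rate: loss x becomes x(1 + f × 8/12), so x must be at least 15/(1 + f × 8/12).

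| Extension rate | Week-12 loss needed (kg) | All eligible extend | Half extend |
|---|---|---|---|
| 0.1 kg/week | 14.2 | 0.151 (3.0 of 20) | 0.136 (2.7 of 20) |
| f = 0.25 | 12.86 | 0.209 | 0.165 |
| f = 0.5 | 11.25 | 0.294 | 0.208 |
| f = 1 | 9.00 | 0.434 (8.7 of 20) | 0.278 (5.6 of 20) |

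With uptake u, P = 0.122 + u × (P at full extension - 0.122). If nobody extends, there is no shift.

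**Composite.** Someone who crosses 15 kg during the extension changes the composite only if HbA1c had not already qualified. Let h be the share with HbA1c below 48 off treatment among those under 15 kg at week 12. The document gives no h, so the values below are illustrative. At f = 1 and full uptake the weight shift is 0.434 - 0.122 = 0.312.
- If HbA1c response is unrelated to weight lost among those under 15 kg, the composite shift is (1 - h) × 0.312: 27, 22 and 12 points for h = 0.12, 0.30 and 0.60.
- If all HbA1c responders are among those who had lost 9 to 15 kg, it is 0.312 - h × 0.878, not below zero: 21, 5 and 0 points.

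The truth probably lies between these two, since the protocol's premise is that weight loss drives remission. HbA1c gains during the extension would add to the shift and are not modelled.

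**Early exit.** A loss of 15 kg is 15/height² BMI units: 5.9 at 1.60 m and 4.9 at 1.75 m. A participant entering below about 22 + 5.9 = 27.9 or 22 + 4.9 = 26.9 respectively falls under BMI 22 before losing 15 kg. Entry is open from just above 25, so the rule can apply. It works against the endpoint and is not in the table.

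**Timing against control.** Three months is about 13 weeks, so a week-20 reading falls 20 - 13 = 7 weeks after the control reading.

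**The case against.** The strongest reply is that this is a choice of question. Section 4 builds the flexible length into the intervention, and the endpoint names the end of that stage. The share at target when a flexible stage ends is a coherent measure of programme response, and Section 6 says that the study is not powered for a primary outcome. That stands: end of TDR is worth reporting. It does not make the figure a 3-month result or stop reading time depending on outcome. Section 1.1 speaks of a 3-6 month phase, which would cover week 20, but it is background and does not replace the objective.

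A reader might infer that the remission test in Section 6.1 is biased by mismatched control timing. The document does not support that. The test pools immediate and delayed participants and compares them with an external 12%, so the control arm's 3-month reading does not enter it. The mismatch matters only for a randomised comparison, which the rationale implies but for which no test of the composite is fixed.

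A reader might also take 43%, or a composite shift of 27 points, as the expected inflation. Neither is supported. The first needs every eligible participant to extend for all 8 weeks at an undiminished rate, while Section 4 only permits extension. The second also needs HbA1c response to be unrelated to weight lost.

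Finally, weight is already scheduled at week 12 and Appendix A ticks bloods there, so much of the remedy exists. That makes the fix cheap, but no text makes week 12 the reading for extenders.

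**Conclusion.** The point holds. The endpoint's reading time depends on its own weight criterion, and for extenders the result is neither the 3-month result in the objective nor matched in time to the control reading. It should be corrected, although the design is not invalidated by it.

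The size is unknown. On the weight criterion alone, 12% at week 12 becomes 15% to 43% with full uptake, 14% to 28% with half uptake, and stays at 12% with none. These figures rest on normality, the Section 6.1 example (mean 8 kg, SD 6 kg), full 8-week extensions and the assumed range of rates. The effect on the composite through the weight criterion is smaller, because some who cross 15 kg late will already qualify on HbA1c. It cannot be fixed from the document.

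**What to change.** 1. State in the Synopsis endpoint, Section 4.1 (Appointments 2-7) and Section 4.3 that weight, HbA1c and glucose-lowering treatment status are taken at week 12 from TDR start for every participant, whether TDR continues, ends or ended early. Repeat them at end of TDR if that is later.
2. Use the week-12 composite (at least 15 kg loss and/or HbA1c below 48 off treatment) as the 3-month result, and in any randomised comparison with the control 3-month reading. Do not call it remission: with drugs stopped at week 0 or week 0+1, week 12 is 11 to 12 weeks off treatment, short of the Section 4.2 definition.
3. Report the end-of-TDR percentage alongside it as programme response, with weeks of TDR completed.
4. Report remission as defined in Section 4.2 from the actual final appointment at the end of food reintroduction, and give its timing. The nominal week 0+19 will not serve for a full extender, who is still on TDR then. With food reintroduction of 2 to 8 weeks, the final visit falls at weeks 14 to 20 after 12 weeks of TDR and weeks 22 to 28 after 20 weeks.

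The extension and the BMI 22 rule stay as they are.

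**Cost.** A protocol amendment; one extra HbA1c per extender (at most about 18 of 20 under the Section 6.1 example) or early leaver; and an extra attendance for it under COVID-19 restrictions, when week-12 weight may not be clinic-measured. Any extender already past week 12 may lack that HbA1c and should be reported as missing it. The 3-month percentage may be lower than the end-of-TDR one.
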